# Study Synopsis

| Company: | ID Biomedical of Québec |
| --- | --- |
| Trial Number: | IDB - 13005 |
| Finished Product: | FluInsure Proteosome – Trivalent Influenza Vaccine |
| Active Ingredient(s): | Hemagglutinin (HA) from each of A/New Caledonia /20/99 (H1N1), A/Panama/2007/99 (H3N2), and B/Shangdong/7/97 viruses and meningococcal outer membrane proteins |
| Title of the Trial: | A Phase II Randomized, Double-blind, Placebo-Controlled Study of Three Regimens of FluINsure™ Proteosome-Trivalent Influenza Vaccine Delivered by the Intranasal Route to Healthy Young Adults, Followed by Intranasal Challenge with Virulent Influenza A Virus |
| Development Phase: | Phase II |
| Principal Investigator: | [name], BSc (Hons), MRPharmS, PhD |
| Co-Investigator: | [name], BSc (Hons), PhD |
| Medical Investigator: | [name], BSc (Hons), MB (Hons), PhD, MRCP |
| Trial Centers: | Retroscreen Virology Ltd., London |
| Planned Trial Period: | Approximately three months to complete screening; two months to complete enrollment, treatment and detailed safety assessment; approximately nine (9) days of inpatient confinement for challenge, final follow-up 11 -19 days post discharge. |
| Objectives: | 1. To evaluate safety and tolerability of FluInsure when delivered intranasally in **three** different regimens to healthy adults, 18 – 50 y.o., selected for pre-existing susceptible immune status with regard to A/Panama//2007/99  2. To evaluate the magnitude of immune responses, in the serum and mucosal compartments, to FluInsure given in three different regimens.  3. To develop preliminary data regarding the protective efficacy of FluInsure by evaluating reduction in influenza-like illness and viral shedding following intranasal challenge with virulent A/Panama/2007/99 |
| Trial Design: | Immunization: Randomized, blinded, and placebo-controlled; featuring the following treatment groups:   1. 15 g of each of the three HAs, IN x 2, (N = 28) 2. 30 g of each of the three HAs, IN x 1, and buffered saline placebo IN x 1 (N = 28) 3. 30 g of each of the three HAs, IN x 2 (N = 28) 4. Buffered saline placebo, IN x 2 (N = 28)   Challenge: Intranasal challenge of approximately 100 subjects randomly drawn from each of the above four treatment groups at 42days (± 7) after the first test article dose. Challenge will be administered by nasal drops containing viable, egg-grown A/Panama/2007/99 |
| Planned Sample Size: | Up to 112 healthy adult volunteers treated, approximately 100 challenged |
| Inclusion Criteria: | 1. Age 18 to 50 years 2. Good general health status as determined by screening evaluation no greater than 42 days prior to immunization 3. Comprehension of the study requirements, including willingness to forego the licensed 2003 – 2004 intramuscular influenza vaccine until protocol participation is complete; expressed availability to fulfill the study requirements; signed informed consent 4. For female subjects, provision of a history of reliable contraceptive practices 5. Serum reciprocal hemagglutination inhibition titer for A/Panama/2007/99 of ≤10 at screening prior to the immunization phase |

| Exclusion Criteria: | 1. Presence of significant acute or chronic, uncontrolled medical or psychiatric illness; significant abnormalities in baseline serum chemistry, hematology, or urinalysis parameters 2. Inadequate venous access for study phlebotomies 3. Positive serologic test for HIV, or **evidence of illicit drug use by urine screening,** 4. In female subjects, a positive urine -HCG on the day of any test article dose or virus challenge 5. Chronic use of any medication or other product, prescription or over-the-counter, for symptoms of rhinitis or nasal congestion, or any chronic nasopharyngeal complaint 6. Any history of asthma of any etiology in adulthood 7. Smokers unwilling/unable to desist for the inpatient component of the trial 8. Acute use of any medication or other product, prescription or over-the-counter, for symptoms of rhinitis or nasal congestion within seven (7) days prior to the first test article dose 9. Abnormal ECG 10. Any anatomic or neurologic abnormality impairing the gag reflex or conducive to aspiration, or history suggestive of such a problem 11. Receipt of systemic glucocorticoids (in a dose  5 mg prednisone daily or equivalent) within one month, or any other cytotoxic or immunosuppressive drug within six months 12. Receipt of any investigational drug within one month, or participation in a clinical trial of any influenza vaccine or any influenza challenge within one year 13. Presence of any febrile illness or significant symptoms of upper respiratory infection on the day of immunization or between admission for influenza challenge and administration of the challenge inoculum 14. History of hypersensitivity to mercurials or chicken eggs |
| --- | --- |
| Investigational Product: | FluINsure Proteosome Trivalent Influenza Vaccine:  Form: liquid (**0.9** mL per 3 mL vial)  Dose: either 15 μg or 30 μg of each of three (3) influenza hemagglutinins complexed to proteosomes, total volume administered will be 0.28 mL by nasal spray  Route: Intranasal  Lot number: 1066  Each vial contains:   1. 150  30 g / mL of hemagglutinin (HA) from *each* of A/New Caledonia/20/99 (H1N1), A/Panama/2007/99 (H3N2) and B/Shangdong/7/97 viruses, non-covalently bound to outer membrane proteins (OMP) of *Neisseria meningitidis* strain 8047 (OMP to HA ratio is approximately 4:1). 2. 10 mM Na/K phosphate-buffered isotonic saline, pH 7.4, with 0.01% thimerosal 3. Non-hemagglutinin viral proteins 4. Trace amounts of egg proteins |
| Control Product: | Phosphate buffered normal saline diluent / placebo:  Form: liquid (10 mL per 20 mL vial)  Dose volume: 0.28 mL by nasal spray  Each vial contains:  10 mM Na/K phosphate-buffered isotonic saline, pH 7.4, with 0.01% thimerosal |
| Challenge: | A/Panama/2007/99, lot I B 44/3, prepared in eggs in compliance with GMP, sterile and mycoplasma-free |
| Trial Time Lines: | Screening in March 2003. Immunization in June 2003. Challenge July 2003. |

| Study Schedule | Test article administrations will occur on immunization phase days 0 and 14 (± 1). Clinical evaluations will be performed at screening, before and after each test article dose, and at days 28 (± 3) and 39 (± 3) . Specimens for clinical chemistry, hematology and urinalysis will be collected at screening (prior to day 0) and on day 28 (± 2). Specimens for assessment of immune response will be collected at screeningand on days 28 (± 2) and 40.  Subjects will be admitted to an inpatient challenge facility 39 ± 3 days after the first immunization and be observed for signs of spontaneous illness for 48 hours. On the morning of the second full challenge phase day, the intranasal challenge will be administered. Subjects will undergo temperature monitoring four times daily, provide twice-daily symptom reports based on a standardized questionnaire of influenza-like symptoms, and have a daily physician examination from the evening of the second challenge day through the afternoon-evening of the ninth challenge phase day. In addition, daily nasal washes and throat swabs will be performed to monitor virus shedding. On the morning of the eighth challenge phase day, subjects will begin treatment with a neuraminidase inhibitor to ensure virus clearance prior to discharge. A follow-up visit on the 20th to 30th challenge phase day will include a clinical evaluation and serum sampling for antibody responses to the challenge agent.  A detailed study schedule appears in appendix B. |
| --- | --- |
| Follow-up Duration: | Volunteers will be followed for 60-70 days after the day 0 immunization. |
| Assessment Methods: | 1. Standard clinical parameters for evaluating the safety of a biologic or vaccine product including: standardized diaries/questionnaires for local and systemic vaccine reactions, repeated vital signs and physical examinations, 60-70 day follow-up for adverse events and concomitant medication changes, monitoring of clinical chemistries (liver and renal function), urinalysis, and hematology.   2. Immunogenicity assessments will include serum hemagglutinin-inhibiting (HAI) antibody specific for the three viruses included in the vaccine, and levels of secretory IgA for these viruses present in nasal wash fluids. In addition, whole blood samples will be used to assess cellular cytokine responses to stimulation with influenza viral antigen.  3. Evaluation of challenge induced influenza will include repeated vital signs and examinations of the ears, nose, throat and lungs. In addition, a standardized symptom questionnaire will be administered twice daily. Once-daily nasal washes and throat swabs will be performed for **detection and / or quantitation of influenza virus using culture, antigen detection and / or molecular biology techniques.** |
| Statistical Methods:  Statistical Methods (cont’d.) | Demography: descriptive statistics will be provided.  Vaccine reactogenicity: Analyses concern graded severities for local and systemic reactogenicity: Comparing one group with another during a treatment period (the design has two periods following the first and second test article exposures), these are two-sample, cross-sectional comparisons of binary, ordinal, or continuous data. Comparing a group with itself between periods, these are paired, repeated measures data. Two-sample, cross-sectional comparisons are based on Fisher’s exact and Cochran-Mantel-Haenszel tests for binary and ordinal outcomes, respectively. Student’s-t and Wilcoxon tests are used for continuous outcomes. These methods permit statistical tests to address the following topics:   - 1. comparison of active and placebo after test article dose 1   2. comparison of active and placebo after test article dose 2, with and without testing for the impact of, and adjustment for, outcomes after dose 1   3. comparison of active and placebo in successive test article doses   4. comparison of placebo in successive test article doses   5. comparison of change from active to active with change from placebo to placebo   Items c. and d. are paired comparisons, which may be performed by McNemar tests or, more flexibly, by GEE models with a binary or continuous outcome. Items b. and e. are tests of interaction: dose 1 by dose 2 in item b., and period by vaccine in item e. and also accessible by GEE models.  Adverse events: Adverse events will be tabulated by body system using the COSTART dictionary, by severity, by seriousness, by relationship to study drug, and by elapsed time since last exposure to study drug. This yields primarily binary data (for each subject, the given COSTART event did or did not occur) which may be analyzed in the same manner as the binary reactogenicity events.  Vital signs & clinical laboratory measures: Mean values and S.D.s will be plotted separately by treatment group. Extreme values and/or outliers will be discussed individually. For clinical laboratory measures within cross-over groups, quantitative outcomes at baseline and day 28 will be compared by paired Student’s t-tests and Wilcoxon signed rank tests. Binary outcomes will be compared by McNemar’s tests.  Immunogenicity: Immunogenicity measures will include serum hemagglutination-inhibiting (HAI) antibody titers specific for the strains included in the vaccine, levels of secretory IgA (sIgA) specific for these viruses in nasal wash fluids. For the HAI titers, analyses will concern geometric mean titers (GMT), proportions of subjects with titer ≥ 40, and proportions with  four-fold increase over baseline. For specific sIgA levels, analyses will concern geometric means and fold-rise from baseline. HAI GMTs and geometric mean nasal specific sIgA levels will be accompanied by 95% confidence intervals. Comparing active-to-placebo and active-to-active groups, titers/antibody levels will be contrasted on day 28 by t-tests on log10(titer). Within the groups, paired tests will be used (Student’s t and Wilcoxon signed rank). Fold-rises may be examined with and without covariate-adjustment for previous titers. Without such adjustment, there are two binary fold-rise outcomes, and these are compared within and between groups by chi-square and stratified chi-square tests. (In the latter case, 2 x 2 tables of treatment by outcome are stratified by previous titers.) With covariate adjustment, the fold-rise outcome is the log10-ratio of early and later titers. Adjustment after the first treatment is for pre-treatment titer and adjustment after the second treatment is for both baseline titer and for titers after the first treatment.  Response to viral challenge: The analysis concerns between-group comparisons of the three groups regarding clinical and immunologic binary outcomes. Alternative definitions provide six binary clinical outcomes that can be compared between groups by chi-square tests. More flexible analyses use logistic regression (with the presence or absence of illness, separately for each definition, as the outcome. Covariates are cross-over study group, age, gender, race, and, for some models, titers after vaccinations 1 and 2.  Additional analyses will be based on illness score and on virus shedding assessed by two methods: peak and a time-weighted average calculated as a trapezoidal-rule AUC. For both peak and AUC, viral shedding is in units of log10(titer). These continuous data will be compared between cross-over groups by Student’s t-tests and Wilcoxon tests and, in a more flexible analysis, by linear model adjusted for the demographic and clinical covariates cited above.  Finally, the three binary measures of influenza and the two viral load estimates (peak titer and AUC) will be assessed relative to the two immunologic measures, HAI reciprocal titer and nasal secretory IgA. For the binary measures, mean viral load (for each measure) is compared by t-tests between those with and without influenza (for each definition). For the two immunologic measures, the test of association with viral load will be based on Pearson correlations of log-titers. |

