During natural infection influenza viruses gain entry through, and are essentially restricted to, respiratory mucosal surfaces. Consequently, mucosal immunity is a pivotal element in controlling these respiratory viral infections. The mucosal immune system consists of an integrated network of lymphoid cells working in concert with the innate mucosal barriers to promote host defense. The humoral arm of the mucosal immune system is comprises principally locally-synthesized polymeric IgA antibodies. Secretory IgA (sIgA) constitutes the majority (>80%) of all antibodies produced in mucosae-associated lymphoid tissues in humans and forms a first line of immune defense. The induction of sIgA antibodies has a key role in the *prevention* of mucosae-restricted respiratory infections. Secretory IgA functions in host defense have been demonstrated at three levels: a) in the lamina propria IgA antibodies bind antigens and cause them to be cleared into the lumen (11); b) antiviral IgA antibodies in transit through epithelial cells inhibit virus production by an intracellular action (12); and c) IgA antibodies secreted into the lumen can prevent antigens from adhering to and penetrating the epithelium (13). The mucosal immune response, as monitored by specific sIgA in the nose, has been shown to be a strong correlate of reduced infection rate, limited viral replication, and reduced illness in influenza challenge studies in adults (1, 6).

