### 7.2.6 Specific Immune Response Assays :

 Serum will be obtained for influenza-specific special serologies (serum hemagglutination-inhibition titers) at the First Screening Visit (A/Panama/2007/99 only), at the Immunization Phase Day 0 visit (all three strains tested for this and subsequent samples), and on Immunization Phase Day**,** 28 (± 3), Challenge Phase Day 0, and Challenge Phase Day 20 - 30.Should hemagglutination-inhibition prove unworkable for the influenza B virus component, single radial hemolysis assay may be utilized.

- Nasal washes for influenza-specific secretory IgA by ELISA will be obtained at the Second Screening Visit (all three strains tested for this and subsequent samples), and on Immunization Phase Day**,** 28 (± 3), Challenge Phase Day 0, and Challenge Phase Day 20 - 30.
- Whole blood will be obtained for *in vitro* cytokine stimulation studies on Immunization Phase Day 0 and Immunization Phase Day28 (± 3).

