Additional secondary analyses will be based on tissue counts (and weights, if feasible) as a marker of illness severity, and on virus shedding assessed by two methods: peak and a time-weighted average calculated as a trapezoidal-rule AUC. For both peak and AUC, viral shedding is in units of log10 (titer). These continuous data will be compared between cross-over groups by Student’s t-tests and Wilcoxon tests and, in a more flexible analysis, by linear model adjusted for the demographic and clinical covariates cited above.

Finally, the three binary measures of influenza and the two viral load estimates (peak titer and AUC) will be assessed relative to the two immunologic measures, HAI reciprocal titer and nasal secretory IgA. For the binary measures, mean viral load (for each measure) is compared by t-tests between those with and without influenza (for each definition). For the two immunologic measures, the test of association with viral load will be based on Pearson correlations of log-titers.

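### The adjusted challenge models omit baseline A/Panama nasal sIgA, which is already measured before dosing and plausibly prognostic; adding it would gain precision at almost no cost

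*Protocol*

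**What the plan says.** The Study Synopsis (Statistical Methods, response to viral challenge) and Section 9.3.8.2 give the same list for the logistic illness models: "Covariates are cross-over study group, age, gender, race, and, for some models, titers after vaccinations 1 and 2". Section 9.3.8.2 then analyses tissue counts and peak and AUC shedding "by linear model adjusted for the demographic and clinical covariates cited above". These regressions are the more flexible analyses. The tests listed before them are chi-square for illness, and t and Wilcoxon for the continuous outcomes.

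Section 7.2.6 states: "Nasal washes for influenza-specific secretory IgA by ELISA will be obtained at the Second Screening Visit", with all three strains assayed. Sections 5.1 and 7.1.2 and Appendix B Table B.1 agree. The window is days -90 to -5.

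On relevance, Section 1.0 says of mucosal immunity, measured by specific nasal sIgA, that it "has been shown to be a strong correlate of reduced infection rate, limited viral replication, and reduced illness in influenza challenge studies in adults". No time point is attached to that statement.

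Entry limits only serum antibody: "Serum reciprocal hemagglutination inhibition titer for A/Panama/2007/99 of ≤10 at screening prior to the immunization phase". Nasal sIgA is not restricted, and the randomisation lists are specific to gender only (Sections 5.1.1 and 6.4.1).

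**The concern.** Selecting on low serum HAI narrows serum susceptibility by design but leaves mucosal immunity free to vary. With about 25 challenged per group (Section 4.1), a chance difference between arms in pre-existing mucosal immunity carries into the estimated reduction in illness and shedding whenever that immunity is prognostic. The adjusted models are where this could be taken out, and the protocol closes their covariate list without the relevant measurement. The point is therefore a stated choice, not a detail left to a later document.

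The antibody terms that are listed cannot stand in for it. Post-vaccination titers lie on the path from vaccine to protection, so adjusting for them changes the question from the effect of the regimen to whatever effect remains beyond the measured response. Sections 7.2.6 and Table B.1 also schedule no antibody sample between the two doses, so a separate titer after the first vaccination will not exist. The protocol accepts baseline adjustment elsewhere: Section 9.1 allows fold-rises to be adjusted for baseline titer.

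**Working it through.** **1. The plan's own figure.** Section 9.3.8.1 claims power of at least 0.80 with 28 per group for a 70% reduction from a 50–60% control rate. With the pooled-variance formula, two-sided 0.05, and p̄ the mean of the two rates:

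power = Φ{[|p₁−p₂|√n − 1.96√(2p̄(1−p̄))] / √(p₁(1−p₁)+p₂(1−p₂))}

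For 0.50 v 0.15 this is Φ[(0.35×5.29 − 1.96×0.662)/0.614] = Φ(0.90) = 0.816. For 0.55 v 0.165 it is 0.873, and for 0.60 v 0.18 it is 0.919. The claim reproduces and uses no covariate. (At 25 per group the 50% case gives 0.77. That is a separate matter.)

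**2. Chance imbalance.** With 25 per arm, the standard error of the between-arm difference in a baseline covariate is √(2/25) = 0.28 SD. At a covariate–outcome correlation ρ of 0.3 or 0.5, an imbalance of that size shifts a continuous contrast by 0.3×0.28 = 0.08 SD or 0.5×0.28 = 0.14 SD. The unadjusted standard error already allows for this, so it is lost precision and not bias.

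**3. Linear shedding models.** Adjustment multiplies the residual SD by √(1−ρ²). Take an effect with 80% unadjusted power at 25 per arm: (1.96+0.84)×0.28 = 0.79 SD. The values of ρ are assumed, because the protocol gives none.

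| ρ | SD factor | Adjusted power | Equivalent arm size, 25/(1−ρ²) |
|---|---|---|---|
| 0.2 | 0.980 | 0.82 | 26 |
| 0.3 | 0.954 | 0.84 | 27 |
| 0.4 | 0.917 | 0.86 | 30 |
| 0.5 | 0.866 | 0.90 | 33 |
| 0.7 | 0.714 | 0.975 | 49 |

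**4. Logistic illness models.** Two arms of 25 were simulated with one normal baseline covariate, marginal illness rates held fixed, and likelihood-ratio tests with and without the covariate (4,000 runs per cell, Monte Carlo error about 0.7 point). The odds ratio per SD is assumed.

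| Odds ratio per SD | 0.50 v 0.15, unadjusted → adjusted | 0.60 v 0.18, unadjusted → adjusted |
|---|---|---|
| 1.0 | 0.78 → 0.79 | 0.91 → 0.90 |
| 1.5 | 0.79 → 0.81 | 0.90 → 0.90 |
| 2 | 0.79 → 0.82 | 0.90 → 0.92 |
| 3 | 0.78 → 0.85 | 0.90 → 0.94 |
| 4 | 0.79 → 0.88 | 0.90 → 0.96 |

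At 0.50 v 0.15 the gain is about 1 to 3 points for odds ratios of 1.5 to 2, and about 7 to 9 for 3 to 4. At 0.60 v 0.18 it is 0 to 2 and about 4 to 5. The simulation left out age, gender and race. If these share information with sIgA, the gain is smaller.

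**5. Room in the illness model.** At 0.50 v 0.15, 25 per arm gives about 12.5 placebo illnesses and 3.75 in an effective arm. If all three regimens work, that is 12.5 + 3×3.75 ≈ 24 events. Three group terms plus age, gender and race (counted as one term) make six, or about 4 events per term. A seventh term leaves about 3.4.

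**6. Age of the sample.** Challenge is on day 41 ± 3 (Section 5.2). The wash is then 38+5 = 43 to 44+90 = 134 days old.

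**The case against.** The case for leaving the list alone has several sound parts.

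- **Time point.** A reader might infer that the protocol calls the pre-vaccination level a strong correlate. It does not: the statement concerns the mucosal immune response in general. Section 1.0 adds that the relative roles of serum and nasal antibody in protection by non-living mucosal vaccines are not settled.
- **Distance from outcome.** The wash is weeks to months old at challenge, and three of four arms meanwhile receive a vaccine expected to raise mean nasal sIgA two- to four-fold. Baseline may predict less well there than in placebo recipients. This stands and pulls the likely gain down the range.
- **Ranking of predictors.** A reader might infer that sIgA is the strongest baseline predictor and the demographic ones weaker. The documents give no strength for any of them, and gender has its own place because randomisation uses it.
- **First-listed tests.** The chi-square, t and Wilcoxon comparisons are valid under randomisation and would not change.
- **Purpose.** Section 9.0 says the trial will not supply definitive evidence, and nasal sIgA is examined against viral load in Section 9.3.8.2.

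What remains is narrower. The viral-load association is not an adjustment of the group contrast. The sparse-event objection applies to the logistic models and is met by substituting a term; the linear shedding models can take one more covariate without difficulty. A small expected gain is still worth having when the measurement is already scheduled.

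**Conclusion.** The point holds as a cheap gain in precision, not as an error in the plan. The covariate list as fixed leaves out a baseline measurement that the protocol collects in every subject and that its own rationale makes plausibly prognostic.

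The size rests on assumed strengths. It is about 1 to 3 power points if baseline sIgA is a weak to moderate predictor (odds ratio 1.5 to 2 per SD, or correlation about 0.2), nearly 4 at correlation 0.3, and about 7 to 10 if strong (odds ratio 3 to 4 at 0.50 v 0.15, or correlation 0.5). If it carries no information, nothing is gained.

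A reader might go further and conclude that the efficacy contrasts are biased or that the power statement fails. Neither follows. Randomisation protects the contrasts, and the power figure involves no covariate. Nor does the omitted variation act as residual noise in every model. That is literal only for the linear ones; in logistic regression the omission costs power and draws the odds ratio towards 1.

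**What to change.** In the Study Synopsis and Section 9.3.8.2, before unblinding:

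- name log10 A/Panama-specific nasal sIgA from the Second Screening Visit, normalised as in Section 9.1, as a covariate in the linear models for peak and AUC shedding;
- name it in the logistic illness models too, preferably in place of age or race given the few events, and keep gender because it is used in randomisation;
- reserve post-vaccination titers for the correlate analyses and take them out of the models that estimate regimen effects.

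The cost is wording and one degree of freedom where the term is added and not substituted. No new sample, assay or visit is needed. The age of the wash at challenge may reduce the gain but does not bias the comparison.
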